9.3.4.1 Definition of Serious Adverse Events

Serious Adverse Events (SAE) refer to any adverse medical condition that occurs during the treatment process and meets one of the following criteria:

(1) Lethality (causing death; note: death is the consequence, not the event);

(2) Life-threatening (Note: "Life-threatening" refers to the immediate danger of death to the patient at the time the event occurs, and does not refer to a hypothetical situation where a more severe event could lead to death.)

(3) Leads to hospitalization of the patient or an extended hospital stay;

(4) Resulting in lifelong or severe disabilities/functional impairments;

(5) It is of significant importance in medicine or requires intervention measures to prevent the occurrence of any of the aforementioned consequences.

9.3.4.2 Causal Relationship

The following standards should be used to assess the relationship between adverse events and treatment:

(1) Very likely related: This category refers to adverse events that are considered to be related to clinical research with a high degree of certainty. An adverse event can be deemed "very likely related" if it meets the following criteria:

The occurrence of adverse events is reasonably time-related to the intervention measures.

The known patient disease status, environmental or toxic factors, or other treatments used by the patient cannot reasonably explain the adverse events.

(2) Possibly related (must meet the first two criteria): This category refers to adverse events that are unlikely to be related to this study, but cannot be definitively ruled out as having a connection. An adverse event can be considered "possibly related" if it meets the following criteria:

The occurrence of adverse events is reasonably time-related to the intervention measures.

Adverse reactions may be caused by the patient's disease state, environmental or toxic factors, or other concomitant treatments used by the patient.

(3) Possibly unrelated (must have the first two items): This category applies to adverse events that meet the following criteria:

The occurrence of adverse events is not reasonably correlated in time with the intervention measures.

Adverse events are clearly caused by the patient's disease state, environmental or toxic factors, or other concomitant treatments used by the patient.

(4) Irrelevant: This category refers to adverse events that are clearly and unequivocally determined to be caused solely by external factors (such as diseases, environment, etc.) and do not meet the relevance judgment criteria under "possibly irrelevant," "possibly relevant," or "very likely relevant."

It must comply with the ICH guidelines for the management of clinical trial safety data and the definitions and standards for expedited reporting.

9.3.4.3 Expected Adverse Events

(1) Epileptic seizure;

(2) fainting;

(4) Localized pain, headache, discomfort;

(5) Temporary changes in hearing;

(6) Brief cognitive/neuropsychological changes;

(7) Acute mental changes;

(8) Others.

9.3.4.4 Adverse Event Handling Measures

(1) Take necessary treatment measures based on specific circumstances and decide whether to terminate the clinical trial. Detailed records of the symptoms, signs, or laboratory test results, including the time of occurrence, duration, severity, management measures, and progress, should be documented in the medical record. The researcher should evaluate the relevance to the clinical trial, sign, and date the record.

(2) When adverse events are discovered, researchers should immediately address the situation and report it to the project leader, the ethics committee, and the clinical research center. They should determine the necessary diagnostic and treatment measures based on the patient's condition and decide whether to terminate the clinical trial. All adverse events should be investigated and tracked, with detailed records of the handling process and outcomes maintained until the issue is properly resolved or the patient's condition stabilizes. If there are abnormal test results, they should be monitored until they return to normal. The method of follow-up can be chosen based on the severity of the adverse reaction, including hospitalization, outpatient visits, home visits, phone calls, or correspondence.

(3) Reporting of Adverse Events: During the study period, regardless of the treatment received by the patient, any serious adverse events or serious laboratory test result abnormalities that occur must be documented by the investigator on an adverse event report form and reported to the project leader, ethics committee, and clinical research center within 24 hours of becoming aware of them.

SAE report contact person: [name](Chengdu Anorectal Hospital Pelvic Floor Center)

Contact person: [name](Academic Committee of Chengdu Anorectal Hospital)

Mobile phone：[name]

Email：[contact]

Address: [name].

(4) Recording: Researchers should document the subjects' symptoms, signs, laboratory tests, the time of onset of damage, duration, severity, treatment measures, and progress in the original medical records and CRF forms, ensuring that the records are true, accurate, complete, timely, and legal. They should fill out the serious adverse event report form, sign it, and indicate the date; the original records should include the time, reporting method, and the reporting institution.

(5) Follow-up: Researchers should follow up on all adverse events experienced by the subjects, determining the follow-up time based on the condition. During the follow-up process, necessary interventions and treatments should be provided to ensure that the harm to the subjects is minimized and to fully guarantee their safety. Detailed records of the follow-up process and the outcomes of the interventions should be maintained.

9.3.5 Emergency Response Measures:

(1) Measures for handling public health emergencies:

Report: During normal working days, on-duty medical staff should immediately report any incidents of harm to subjects to the incident handling team. On holidays or at night, they should report immediately to the administrative duty officer, who will then report to the subject harm and incident handling team. The team members should conduct a comprehensive assessment, make a preliminary judgment on the nature of the public health emergency, and report to the higher administrative department, suggesting whether to activate the emergency response plan for public health incidents.

(2) Activate the emergency plan: After approval from the higher health administrative department, activate the emergency plan for public health emergencies, including:

★ Establish special outpatient services, emergency services, and observation rooms.

★ Hospital leadership duty: The hospital office quickly formulated a duty schedule for the hospital leaders, ensuring that one leader is on duty 24 hours a day, fully responsible for emergencies; the medical department has dedicated personnel on duty 24 hours a day; all relevant personnel have their mobile phones on 24 hours a day to ensure smooth communication. Every morning at 8:00 AM and every afternoon at 5:00 PM, gather relevant information at the department, hold a focused discussion, and address related issues.

★ Ensure Material Supply: Urgently mobilize personnel, reserve relevant materials, transportation tools, as well as related facilities and equipment, to ensure the reasonable allocation of medical resources and guarantee the supply of emergency medical materials for key departments.

★ Evacuation or Isolation: Evacuate and isolate personnel as necessary based on the condition.

★ Rescue and Documentation: Medical personnel strictly adhere to protective measures, providing emergency medical care and on-site treatment for patients; they write detailed and complete medical records; if transfer to another hospital is necessary, patients are transferred to the receiving or designated medical institution as per regulations.

★ Training and Drills: Regular training on emergency response knowledge and skills related to the nature of public health emergencies. Drill, always be prepared for emergencies.

(2) Measures for dealing with natural disasters:

In the event of a fire, flood, earthquake, or similar incidents, you should immediately contact "119" or "110" and inform the damage and emergency response team. During holidays or at night, the report should be made to the general duty officer, who will then notify the aforementioned team. The team leader will promptly report to the dean and receive instructions, while the office will announce the emergency situation to the entire institution. Relevant functional departments should carry out their respective duties.

(3) Emergency power and water outage response measures:

Handling measures: In the event of a sudden power outage in a department due to local circuit issues, medical staff should immediately notify the management personnel of the General Affairs Department by phone. After receiving the notification, the logistics management personnel should promptly arrange for professionals to rush to the site for emergency repairs to restore power as soon as possible. Departments should make arrangements in advance for work when notified of water or power outages; relevant inspections or treatments scheduled during that time should be avoided. For specimens that must be tested on the same day as required by the clinical trial protocol, they should be properly preserved while ensuring specimen quality, and testing should be conducted after water or power supply is restored.

9.3.6 Penalties: If medical personnel engage in any of the following behaviors, the relevant department of the hospital shall order corrections, issue a notice of criticism, and give a warning;

Disciplinary actions such as demotion or dismissal shall be imposed on department heads and other directly responsible individuals in accordance with the law; if the consequences result in disability, death, or the spread of disease among subjects (patients), or cause other serious harm to public health, and constitute a crime, criminal responsibility shall be pursued in accordance with the law.

(1) Failure to fulfill the reporting responsibilities for adverse events or emergencies as required, including concealing, delaying, or falsely reporting.

(2) Failure to take timely measures for adverse events or emergencies that occur in subjects as required.

(3) Refusing to see patients when an emergency occurs;

(4) Refusing to comply with hospital work arrangements during emergencies.

10. Recruitment process (including recruitment procedures and start time, recruitment materials, expected number of recruits)

10.1 Recruitment Procedure: This includes three stages: recruiting subjects, screening qualified subjects, and obtaining informed consent from the subjects.

10.1.1 Recruitment of Subjects

(1) Subject recruitment staff: Responsible doctors for patient reception, attending resident physicians, and clinical supervising doctors can also be involved. Once the recruitment personnel are determined, a recruitment plan and requirements will be developed.

(2) Recruitment methods: The first method is for the recruiting personnel to determine that the patient meets the trial requirements and recommend the patient to participate in the trial; the second method is when the patient's attending physician is not a researcher of the trial, the physician determines that the patient meets the clinical trial requirements, inquires about the patient's willingness, and then contacts the researcher to include the patient.

(3) Recruitment locations: hospital outpatient departments, inpatient wards, or health examination centers.

(4) Reception of potential subjects: Set up a dedicated recruitment window with designated personnel responsible for receiving visiting subjects or use a dedicated phone line to answer inquiries from consulting patients.

(5) Make a preliminary judgment on the likelihood of subject inclusion based on the inclusion and exclusion criteria as well as the doctor's clinical experience.

(6) Subject eligibility screening: Provide an overview of the trial to subjects who are initially judged to be potentially eligible, conduct physical examinations or laboratory tests, and based on the results of these examinations, confirm again whether the subjects truly meet the inclusion and exclusion criteria for the trial.

(7) Informed consent of the subjects: A detailed explanation of the clinical trial protocol will be provided to patients who meet the screening criteria, and they will be informed of the potential benefits and risks, ensuring that they are fully informed.

10.1.2 Screening Qualified Subjects

The initial assessment of potentially eligible subjects will be conducted for eligibility determination. A separate, clear, and specific medical history screening form should be designed in advance based on the eligibility criteria. The eligibility criteria involve refining the clinical trial's diagnostic criteria and inclusion/exclusion criteria into assessable items, and excluding special populations (such as pregnant individuals and those with infectious diseases) and patients with related complications based on the disease and trial design. The eligibility criteria will determine whether subjects meet the requirements of the clinical trial; patients who meet the research conditions will enter the clinical trial, while those deemed ineligible will be excluded and not enrolled. Any additional assessment costs incurred for patients who do not meet the requirements should be borne by the research project, and they should receive standard treatment. The specific eligibility determination process is as follows: ① Include subjects who meet the predetermined diagnostic criteria; ② Then include subjects who meet the predetermined inclusion criteria; ③ Finally, exclude patients who exhibit characteristics of the exclusion criteria from those who do not exhibit such characteristics.

10.1.3 Obtaining Informed Consent from Subjects

After passing the eligibility screening, researchers should inform each participant about informed consent and confirm their signature.

10.2 Startup Time

The project will start recruiting participants on January 1, 2024, after obtaining approval and ethics committee approval.

10.3 Recruitment Materials

Informed Consent Form.

10.4 Expected Number of Recruits

66 patients with chronic pelvic pain syndrome accompanied by mental and psychological disorders who meet the selection criteria.

10.5 Time of participation in the study (duration of each participation and total time)

Participants who have been enrolled and received the first week of treatment (5 sessions) are considered to have participated in the study for the first time; participants receive 5 treatments per week for a total of 4 weeks (20 sessions); after the treatment course ends, they return to the hospital 8 weeks later for further examinations and assessments; the total duration of participation in the study ends 8 weeks after the treatment course concludes.

11. Data Management and Statistical Analysis Plan

11.1 Data Processing

11.1.1 Data Collection

All data should be recorded in a timely, truthful, and detailed manner in the Case Report Form (CRF). Researchers must input information into the CRF according to the protocol requirements. The research center will assign a supervisor to check the completeness and accuracy of the CRF and guide the research center staff in making necessary modifications or additions. The CRF will be submitted to data processing by the research supervisor, with one copy retained at the research center and another attached as the supervisor's work document. The CRF will be handed over to two reliable medical data processors for data entry and verification. The case report form should be filled out by a designated person from the unit and signed by the project leader of the unit to be considered a valid case. After the clinical trial is completed, a clinical summary report should be written according to the requirements of the clinical summary guidelines.

11.1.2 Case Report Form (CRF)

In clinical trials, it is necessary to record the specified observations or examination items in the case report form. The case report form includes...

The content must be completely consistent with the original data, and the basis for the results calculated from the original data should be traceable.

When filling out, you must meet the following standards:

(1) Fill in with a black signature pen or black ballpoint pen;

(2) Cases that have already signed the informed consent form and meet the inclusion criteria should fill out the case report form, even if they have not received treatment or are determined to not meet the inclusion criteria after treatment.

(3) When making corrections, the original record must be crossed out with a line (correction fluid or similar cannot be used), but the original record must remain legible. Additionally, the person making the correction must sign at the correction point and indicate the date of the correction.

(4) For unexamined items, it must be marked as "ND (Not Done)".

11.1.3 Database Management and Quality Control

The data items in the CRF will be entered into the research database using a double-entry verification method. Text items (such as comments) can only be manually verified after being entered once from the CRF. Subsequently, data managers conduct systematic checks on the information in the input database using error messages printed from the confirmation procedures and database lists. If necessary, a separate document provides clear instructions for special operations related to the handling and archiving of the DQF (Data Quality Form) for the trial (such as confirmation plans). The database will be locked once it is declared complete and error-free. After that, any changes to the database can only be made with the joint written consent of the clinical research leader, research statistician, and data manager. The interpretation of results will be conducted by a third party who is unaware of the patient grouping, ensuring the objectivity of the results.

11.2 Statistical Analysis

11.2.1 Analysis of Population Definition:

The patients who were enrolled and received treatment constitute the intention-to-treat population (ITT) for this trial. The population and the patients who comply with the requirements of this clinical trial protocol and complete this study constitute the per protocol population (PP). The statistical analysis will use intention-to-treat (ITT) for missing data, comparing the "full analysis set (FAS)" and the "per protocol set (PP)."

11.2.2 Statistical Analysis Methods

Statistical analysis will be conducted using SPSS 27.0 software. Continuous data will be presented as mean ± standard deviation. Paired t-tests will be used for inter-group comparisons, and repeated measures ANOVA will be used for intra-group comparisons, including before and after treatment and during follow-up. Statistical significance will be indicated by a P value < 0.05. If there is a reduction in personnel during the trial, an intention-to-treat (ITT) analysis will be performed, comparing the "full analysis set (FAS)" and the "per-protocol set (PP)."

12. Data Confidentiality Plan

Participation in the trial and personal information during the trial are confidential. Information that can identify the subjects will not be disclosed to anyone outside the research team unless permission is obtained from the subjects. All research members and sponsors are required to keep the identities of the subjects confidential. The subjects' files will be stored in a locked filing cabinet and will only be accessible to researchers. To ensure that the research is conducted according to regulations, government regulatory agencies or members of the ethics review committee may review the subjects' personal information at the research site as necessary. When the results of this study are published, no personal information about the subjects will be disclosed.

13. Ethical Requirements and Informed Consent

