| Abstract | Chronic pelvic pain syndrome (CPPS) has a high incidence and can present with severe symptoms, leading to mental health issues, causing anxiety, depression, and pain catastrophizing, and placing significant stress on families and society. The exact causes and mechanisms of CPPS remain unclear; studies suggest it may be caused by psychological issues and multi-system dysfunction. Therefore, addressing psychological problems is crucial in the treatment of CPPS. Repetitive peripheral magnetic stimulation (rPMS) shows potential effectiveness in treating CPPS, while repetitive transcranial magnetic stimulation (rTMS) has been proven to be effective for anxiety and depression. This study employs a randomized, double-blind method, recruiting 66 CPPS participants with accompanying psychological issues, who are stratified by gender and randomly assigned to three groups (1:1:1): double-target magnetic stimulation group, peripheral magnetic stimulation group, and sham stimulation group, receiving the corresponding treatments. The efficacy and safety of double-target magnetic stimulation in CPPS patients with psychological disorders will be assessed by comparing changes in pelvic pain scores (for females) or the National Institutes of Health Chronic Prostatitis Symptom Index (NIH-CPSI, for males), depression, anxiety, and stress scales (DASS-21), pelvic floor surface electromyography, pudendal nerve motor evoked potentials, and the 36-item Short Form Health Survey (SF-36) scores before and after treatment. | | | | | | | | | | |
| Keywords | | Repetitive Transcranial Magnetic Stimulation, Repetitive Peripheral Magnetic Stimulation, Chronic Pelvic Pain Syndrome, Randomized Controlled Trial | | | | | | | | | |

**三.**Project Team Members (including Principal Investigators)

| Name | Unit | Dgree | Title | Task division | Ethics training | GCP training | Signature |
| --- | --- | --- | --- | --- | --- | --- | --- |
| [name] | Chengdu Anorectal Hospital | Master's degree | Associate Chief Physician | Project Leader | Yes | Yes |  |
| [name] | Chengdu Anorectal Hospital | Doctor | Professor | Project Guidance | Yes | Yes |  |
| [name] | Chengdu University of Traditional Chinese Medicine Affiliated Hospital | Doctor | Chief Physician | Supervision of Project Implementation | Yes | Yes |  |
| [name] | Sichuan Province Fifth People's Hospital | Master's degree | Attending physician | Data organization, statistical analysis | Yes | Yes |  |

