| 1. Features and Innovations of this Project  This study employs a prospective randomized controlled trial design, setting up a control group experiment. The control group will consist of CPPS patients receiving sham stimulation and those receiving peripheral magnetic stimulation, while the experimental group will consist of CPPS patients receiving dual-target magnetic stimulation. By comparing the clinical safety and efficacy indicators among the three groups of patients, the study aims to explore the therapeutic effects and safety of dual-target magnetic stimulation in CPPS patients with comorbid psychological disorders. Dual-target magnetic stimulation is derived from the author's team's years of clinical experience and in-depth understanding of various CPPS treatment methods. Currently, no relevant studies have been found in domestic and international literature regarding the use of this type of treatment for CPPS patients with comorbid psychological issues.   1. Feasibility Analysis (Department Conditions, Personnel Allocation, Case Sources, Technical Conditions, etc.)   Chengdu Anorectal Specialty Hospital is a tertiary first-class specialty hospital that integrates medical treatment, teaching, research, and preventive healthcare into a medical center. Its anorectal department is a nationally key clinical specialty, and the constipation department and pelvic floor center have a significant influence in the western region of China. The treatment for this clinical research will be conducted at the hospital's pelvic floor center.  Our team has accumulated certain clinical experience in the application effects and safety of peripheral magnetic stimulation in the treatment of CPPS. We have established standardized procedures for using transcranial magnetic stimulation to treat mental disorders such as anxiety and depression. According to relevant reports, the incidence of CPPS has shown an upward trend both domestically and internationally, and the presence of psychological issues is a major reason for its poor treatment outcomes. Therefore, it is particularly important to find effective treatment methods for CPPS patients with coexisting psychological disorders.  The research team currently has 5 senior technical staff members, 8 individuals with a master's degree or higher, and possesses rich experience in clinical research, patient follow-up, and statistical analysis. This ensures the accuracy of clinical data recording and statistical analysis. The talent structure is reasonable, with clear division of labor, which guarantees the smooth completion of this project. |

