5.1 Sample Size Estimation

According to the research by Yang Jing-ming and his colleagues, under the conditions of β=0.1 and α=0.05, the effect size is 0.5. Pain scores will be used as the primary measurement standard, and G*Power 3.1.9.7 will be used to estimate the sample size. It is calculated that there will be approximately 54 patients in the study cohort, and considering a 10% dropout rate, each group will include 22 people, requiring a total of 66 participants for this RCT.

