5.2 Patient Number and Randomization Group

Input patient data into the computer to obtain a subject number. All subject numbers will be three digits long, and patients will consistently use this number throughout the study, which will not be reassigned. Patients who withdraw their informed consent or discontinue the study after their patient number has been assigned will retain their initial number. Randomization will be conducted using a stratified block randomization method, stratified by gender, followed by block randomization within each stratum. Since the purpose of this study is to compare the improvement in symptom scores of chronic pelvic pain as well as anxiety and depression scores, gender is an important influencing factor. Therefore, gender will be used as a stratification factor, and block randomization (with 2 blocks per stratum and a block length of 4) will be employed for grouping. The aforementioned stratified block randomization can be implemented using SPSS software.

6. Research steps or treatment plan

6.1 Clinical intervention measures and steps.

(1) Before treatment: Conduct three examinations and seven comparisons. Researchers will carry out a risk assessment.

(2) Stimulation plan: First conduct rPMS, then conduct rTMS.

(3) Stimulation Site: For peripheral stimulation, the center of the circular coil will be aligned with the S3 region. During the stimulation process, if you feel contractions in the perineal muscles and dorsiflexion responses in the feet, it indicates that the position is correct. For central stimulation, the left DLPFC (l-DLPFC) region will be targeted for patients with major depressive disorder, while the right DLPFC (r-DLPFC) region will be targeted for patients with generalized anxiety disorder.

(4) Stimulation intensity: For peripheral stimulation, 50% of the maximum stimulation intensity will be applied. For central stimulation, the setting will be adjusted to 120% of the resting motor threshold (RMT).

(5) Stimulation parameters: ① Peripheral stimulation: 20 Hz, 2 seconds of stimulation, 28 seconds interval, a total of 1600 pulses. ② r-DLPFC: 1 Hz, 10 seconds of stimulation, 2 seconds interval, a total of 1000 pulses. ③ l-DLPFC: 10 Hz, 4 seconds of stimulation, 26 seconds interval, a total of 3000 pulses.

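### The between-arm test is wrong as written: Section 11.2.2 assigns paired t-tests to three independent arms and repeated-measures ANOVA to within-arm change

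*Protocol*

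**What the plan says.** Section 11.2.2 of the protocol states: "Paired t-tests will be used for inter-group comparisons, and repeated measures ANOVA will be used for intra-group comparisons". It ties the second method to measurements before treatment, after treatment and at follow-up, and sets one threshold: "Statistical significance will be indicated by a P value" below 0.05.

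The design is parallel. The abstract in the application form has patients "randomly assigned to three groups (1:1:1): double-target magnetic stimulation group, peripheral magnetic stimulation group, and sham stimulation group". Section 5.2 describes the allocation: "Randomization will be conducted using a stratified block randomization method, stratified by gender, followed by block randomization within each stratum". Neither place mentions matching of individuals.

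The aim is a comparison of arms. The application form, under features and innovations, reaches its conclusion "By comparing the clinical safety and efficacy indicators among the three groups of patients", and Section 14.4 has a blinded statistician compare the three groups.

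Section 5.1 sizes the trial so that "under the conditions of β=0.1 and α=0.05, the effect size is 0.5", and adds: "It is calculated that there will be approximately 54 patients in the study cohort".

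**The concern.** A paired t-test analyses differences within linked pairs. Here no patient in one arm is linked to any patient in another, so the only test the protocol assigns to between-arm comparison has nothing defined to work on. An analyst who followed the sentence literally would have to pair patients by some arbitrary rule, such as row order, and discard patients once dropout left the arms unequal.

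The other method, repeated-measures ANOVA, is assigned to change within an arm. Such change mixes the effect of treatment with natural course, regression to the mean and the placebo response that the sham arm exists to measure.

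At stake is the trial's main question: whether dual-target stimulation does better than sham and better than peripheral stimulation alone. No other section names a test that answers it.

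**Working it through.** **1. What the sample size was built for.** Inputs from Section 5.1: effect size 0.5, α = 0.05, β = 0.1, about 54 patients in total. The effect-size metric and the test are not stated, so candidates were tried.

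- One-way ANOVA, 3 groups, Cohen's f = 0.5: noncentrality λ = f²N = 0.25 × 54 = 13.5, with 2 and 51 degrees of freedom. Power is 90.2%. At N = 53 it is 89.6%, so 54 is the smallest N reaching 90%.
- Two-sample t-test, d = 0.5: 86 per arm two-sided, 70 one-sided.
- Paired t-test, d = 0.5: 44 pairs two-sided, 36 one-sided.
- Repeated-measures ANOVA, f = 0.5, 6 time points, within-patient correlation 0.5 (assumption): N = 33 (between), 9 (within), 12 (interaction).

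Of these, only the independent-groups one-way ANOVA returns 54. Section 11.2.2 does not list it.

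**2. Dependence on row order.** Assumed illustration: 20 per arm, equal SDs, observed difference 0.6 SD.

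- Unpaired: t = 0.6 × √(20/2) = 1.897 on 38 degrees of freedom, p = 0.065.
- Paired: the mean difference is fixed, but its standard error depends on who is matched with whom. Over 5,000 random pairings of the same data the central 95% of p-values runs from about 0.02 to about 0.13, and about 22% are below 0.05 (21% to 24% across simulated data sets).

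The same data can therefore be significant or not according to how the file was sorted.

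**3. Does it inflate type I error?** No. In 100,000 simulated null trials with 18 per arm, arbitrarily paired tests rejected in 4.9% to 5.1% of trials for each contrast, the same as unpaired tests. Degrees of freedom fall from 2n − 2 = 34 to n − 1 = 17, which costs little power: at a true difference of 1.225 SD, 93.3% paired against 94.6% unpaired.

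**4. Within-arm tests cannot stand in.** Assume all three arms improve equally, by 0.5 SD of the change score, with 18 per arm. Each arm's own test is significant in about 51.5% of trials. Dual-target is then significant while sham is not in about 0.515 × (1 − 0.515) = 25% of trials, although there is no treatment effect. At 0.7 SD the figure is about 16%.

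**5. Family-wise error once between-arm contrasts are tested properly.** Unpaired t-tests at one visit, each at 0.05, no true difference:

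- Dual vs sham and dual vs peripheral: about 9% (simulated, 20 per arm).
- All three pairs: about 12% (simulated, 12.2% at 18 per arm). Independent tests would give 1 − 0.95³ = 14.3%; the contrasts share arms, so the true figure is lower.

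**The case against.** The strongest reply is that the two labels were swapped in translation. Paired t-tests within arms and repeated-measures ANOVA between arms would be conventional. The English has other slips, such as adverse events recorded after surgery in a stimulation trial (Section 8.2). The sample size points to a between-group ANOVA, and Section 14.4 plans a three-group comparison. This is plausible, and it means a reader should not infer that no between-arm comparison was intended. It does not rescue the sentence, which is the operative instruction. Swapping the labels would also still leave the between-arm effect and its time point to be named.

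A second reply is that the statistical analysis plan, if there is one, may settle the detail. That holds for multiplicity, covariates and missing visits, which are ordinary contents of such a plan. It does not hold for a test that the protocol states positively and wrongly.

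A third reply is that arbitrary pairing keeps the error rate at its nominal level. That is correct (step 3). The pairing figures show an undefined, order-dependent result, not excess false positives.

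**Conclusion.** The sentence is wrong as written and has to be corrected before analysis. The named between-arm test does not fit three independent arms, the within-arm method does not estimate a treatment effect, and neither matches the one-way ANOVA that reproduces the 54 patients. That match rests on reading the effect size as Cohen's f, which the protocol does not say. The pairing figures rest on an assumed 20 per arm and an observed difference of 0.6 SD.

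Some stronger readings are not supported:

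- A reader might infer that every p-value below 0.05 will count, across three pairs and five post-baseline visits. Section 11.2.2 gives one threshold and lists neither a family of pairwise tests nor visit-by-visit testing.
- A reader might infer that baseline score and sex are wrongly left out of the model. No model formula is given from which they could be missing.
- A reader might infer that patients with a missed visit will be dropped. Sections 11.2.1 and 11.2.2 state an intention-to-treat aim, though loosely, and the method of handling missing visits can be left to the analysis plan.

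**What to change.** Replace the sentence in Section 11.2.2 along these lines: *Arms will be compared with an independent-groups analysis, a linear mixed model with arm, visit, arm-by-visit and baseline score (or ANCOVA at the primary time point). The primary contrasts are dual-target versus sham and dual-target versus peripheral at [one named time point], with Holm or fixed-sequence control at two-sided 0.05. Paired t-tests will be used only to describe change within an arm.* The choice of time point is the sponsor's; the documents give no basis for preferring one.

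A single model on raw scores would not do. Women are scored on the pelvic pain scale (16 items, each 0 to 10, Appendix 3) and men on the NIH-CPSI (overall rating up to 43, Appendix 4). A sex term alone does not put these on one scale. Either standardise the score within sex before pooling, or fit the model within each sex stratum and combine the standardised arm effects. Section 5.1 should also name the test and the effect-size metric, so that sample size and analysis agree.

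The change is to wording only; data and software stay the same. The cost is a somewhat stricter threshold for pairwise claims. As an outer bound, take unpaired t-tests at 18 per arm with f = 0.5 from equally spaced means (assumption). Moving from 0.05 to 0.05/3 lowers power from 94.6% to 86.9% for the extreme contrast (1.225 SD) and from 43.1% to 26.3% for an adjacent one (0.612 SD). Holm over two contrasts costs less, because its strictest step is 0.025.
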